**Methods/Design:**

In this effectiveness-implementation hybrid type I design, 200 HIV+ women with major depressive disorder (MDD) and posttraumatic stress disorder (PTSD) who are receiving care at a Family AIDS Care Education and Services (FACES)-supported clinic in Kisumu, Kenya will be randomized to: (1) interpersonal psychotherapy (IPT) + treatment as usual (TAU) or (2) TAU, both delivered within the HIV clinic. IPT will consist of 12 weekly 60-minute individual IPT sessions, delivered by non-specialists trained to provide IPT. Primary effectiveness outcomes will include MDD and PTSD diagnosis on the Mini International Diagnostic Interview (MINI). Primary implementation outcomes will include treatment cost-benefit, acceptability, appropriateness, feasibility and fidelity of the IPT delivery within an HIV clinic.

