##### Feasibility

The treatment will be considered feasible if the 220 study participants are recruited by screening at least 300 HIV+ GBV+ women, if each completer attends ≥80 % of IPT sessions, attrition is 50 or fewer study participants and if 50 % or fewer of the study therapists voluntarily drop out of the training course and trial.

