#### Implementation

##### Feasibility

The treatment will be considered feasible if the 200 study participants are recruited by screening at least 300 HIV+ GBV+ women, if each completer attends ≥80 % of IPT sessions, attrition is fewer than 50 study participants and if one or fewer therapists voluntarily drop out of the training course and trial.

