##### Feasibility and fidelity

Feasibility and Fidelity measures will be assessed by sample means and proportions, with 95 % confidence intervals, and compared to pre-specified benchmarks (see above).

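### The feasibility screening criterion is a floor of 300 women with no upper limit, so it passes poor recruitment yields and fails good ones

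*Protocol article*

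**What the plan says.** The abstract (Methods/Design) lists feasibility among the primary implementation outcomes. Two paragraphs headed Feasibility, one under Implementation outcomes and one under Statistical analysis, each set four joint conditions:

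- **Screening.** Under Implementation outcomes, "if the 220 study participants are recruited by screening at least 300 HIV+ GBV+ women"; under Statistical analysis, "if the 200 study participants are recruited by screening at least 300 HIV+ GBV+ women".
- **Attendance.** In both, "if each completer attends ≥80 % of IPT sessions".
- **Attrition.** Under Implementation outcomes, "attrition is 50 or fewer study participants"; under Statistical analysis, "attrition is fewer than 50 study participants".
- **Therapists leaving voluntarily.** Under Implementation outcomes, no more than half; under Statistical analysis, no more than one.

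The Recruitment section says that women are screened consecutively until the sample size is reached. The section Feasibility and fidelity says that these measures will be summarised as means and proportions with 95% confidence intervals and set against the benchmarks already given.

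**The concern.** Because recruitment stops when the target is filled, the number of women screened is not chosen in advance. It measures how hard the sample was to find, and fewer screens means easier recruitment. A criterion that demands 300 or more is therefore met more easily as recruitment gets harder, and nothing in the sentence limits how hard it may get.

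The Discussion says that resources are directed to data that will inform scale-up. A feasibility verdict that can be passed on a very low yield, or failed on a very high one, would mislead a clinic deciding whether enough eligible women can be found.

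Two lesser matters sit in the same sentences. The attendance condition looks only at completers, so women who stop therapy do not count in it. And the two paragraphs give different limits, so the later comparison has no single set of benchmarks to use.

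**Working it through.** The benchmarks are stated without derivation, so there is no figure of the plan's own to reproduce. The check is to apply them.

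**Screening.** Inputs: a target of 220 (Randomization; Feasibility under Implementation outcomes) or 200 (abstract; Sample size; Feasibility under Statistical analysis), and the threshold of 300. Yield = recruited / screened. The numbers screened are illustrative, apart from 300.

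| Screened | Yield, target 220 | Yield, target 200 | As written (300 or more) | Reversed (300 or fewer) |
|---|---|---|---|---|
| 250 | 220/250 = 88.0% | 200/250 = 80.0% | fails | passes |
| 299 | 220/299 = 73.6% | 200/299 = 66.9% | fails | passes |
| 300 | 220/300 = 73.3% | 200/300 = 66.7% | passes | passes |
| 600 | 220/600 = 36.7% | 200/600 = 33.3% | passes | fails |
| 1,000 | 220/1,000 = 22.0% | 200/1,000 = 20.0% | passes | fails |
| 3,000 | 220/3,000 = 7.3% | 200/3,000 = 6.7% | passes | fails |

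As written, the rule caps the yield at 73.3% or 66.7% and sets no minimum.

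**Attendance.** The abstract gives 12 weekly sessions, and 0.80 × 12 = 9.6, so the rule means at least 10 of 12. Non-completers are limited only by the attrition cap:

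- Overall, the cap allows 50/220 = 22.7% or 49/200 = 24.5% of participants to be lost.
- It is not specific to an arm. Assuming 1:1 allocation and, as the extreme case, all losses in the IPT + TAU arm, 50/110 = 45% or 49/100 = 49% of that arm could be lost with the cap still met.
- It counts study participants. A woman who stops therapy but still attends assessments may count neither as a completer nor as attrition.

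**The two Feasibility paragraphs side by side.**

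- Target: 220 against 200.
- Attrition: exactly 50 losses passes one and fails the other.
- Therapists: half or fewer against one or fewer. The number of therapists is not given in the article. With 2 or 3 therapists both rules allow one departure; with 4 they allow 2 against 1; with 10 they allow 5 against 1.

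**The case against.** **On the screening bound.** One could read 300 as a commitment to screen at least that many women, a capacity target. That does not rescue the wording: the sentence makes it a condition for calling the treatment feasible, and even on that reading it says nothing about yield. The same wording in two sections also makes an isolated slip less likely. It is fair, however, that the intended bound is nowhere stated. The criterion also counts HIV+ GBV+ women, whereas the Recruitment section screens consecutive HIV+ women, so the denominator is open too.

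**On the benchmarks as a whole.** A reader might infer that they do not measure feasibility at all. The document does not support that. The attrition and therapist criteria are upper limits and point the right way, and a fault in one joint condition does not disable the others.

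**On attendance.** A reader might infer that the completer rule is either automatic (if completion is defined by attendance) or almost unattainable (if a single woman below 80% fails the treatment). That depends on a definition of completer which the full protocol may contain, and on assumed attendance probabilities that the article does not give. The section Feasibility and fidelity already plans proportions with confidence intervals, which favours a graded summary. Attendance among completers together with a cap on losses is a coherent design. What remains is that the cap covers the other women only in part, so reporting on all randomised women is an improvement, not the correction of an error.

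**On importance.** The Sample size section says that effectiveness is the primary goal. Randomisation, power and the MDD and PTSD analyses do not depend on these benchmarks, and numbers screened can be reported whatever the rule says. That argument stands, and it limits the severity.

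**Conclusion.** The screening criterion is wrong as written, in both places. It passes a yield of 7.3% (or 6.7%) and fails one of 88.0% (or 80.0%). This rests only on the literal wording and on the Recruitment section's statement that screening continues until the sample is reached; no outside figure is needed. That the sponsor meant a ceiling of 300, equivalent to a yield of at least 73.3% or 66.7%, is an inference from the sense of the sentence and from the direction of the attrition and therapist limits.

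The attendance point is secondary. The 45% and 49% figures are worst cases under assumed 1:1 allocation and show only that the attrition cap is a partial safeguard. The conflicts between the two Feasibility paragraphs are plain from the text. Overall severity is moderate: a primary implementation outcome has a faulty decision rule, but the effectiveness conclusions are untouched.

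**What to change.** 1. In both Feasibility paragraphs, replace the floor with a maximum number screened or, equivalently, a minimum proportion of screened women who are randomised, reported with a 95% CI. If the intent was no more than 300 HIV+ GBV+ women screened, say so. The sponsor must confirm both the bound and who counts as screened (all consecutive HIV+ women, or only those who are GBV+).
2. Add the proportion of all women randomised to IPT + TAU who attend at least 80% of sessions (10 of 12), with a 95% CI against one stated benchmark. Attendance among completers can stay as a supplementary figure.
3. Reconcile the two paragraphs on the recruitment target, the attrition limit and the therapist drop-out limit, and state the benchmarks once.

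The cost is wording in two paragraphs, plus access to the screening and attendance records that the existing criteria already require. The downsides are that the all-randomised attendance figure will probably look less favourable than the one for completers, and that a low screening yield will now count against feasibility. The article reports that the trial is still recruiting; the change should be dated and made before the feasibility results are known.

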### Interpersonal Psychotherapy (IPT) therapists

There are no formal education or experience requirements for the community therapists who are trained to deliver IPT in this study. All therapists must be women and all must undergo a 10-day training in IPT, similar to the trainings we have undertaken with other traumatized populations in low-resource settings [26, 27]. Therapists will then complete the run-in phase of the study, during which they will be assigned a pilot IPT case. During the pilot phase and throughout the study, each therapist will receive weekly telephone supervision from one of two psychiatrists who are experts in IPT (study principal investigator (PI) and co-investigator), at which time they will be scored on 10 key aspects of delivering IPT, according to the IPT phase in which they are working and using a 10-point Likert scale for each response. Only those therapists who consistently score “9 s” and “10s” by the end of their IPT case will be allowed to progress to work with participants enrolled in the study trial. Therapists who do not meet these criteria will be provided with one or two additional pilot IPT cases. In addition to weekly individual supervision by psychiatrists who are IPT experts, a train-the-trainer model will be used to provide selected IPT therapists with additional training as on-site peer supervisors, including running weekly, onsite IPT group supervision, to be conducted as an adjunct to ongoing weekly telephone supervision from PI and co-investigator during the trial. Ongoing supervision is recognized as a critical hurdle for successful implementation [28] – the IPT peer group supervision will serve as a key implementation resource for sustaining the intervention following the conclusion of the study.

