##### Fidelity

As mentioned above, therapists will discuss each IPT session with an IPT supervisor by telephone and peer IPT supervision group onsite. During supervision, therapists will be assisted with their adherence to and application of IPT. Adherence will be scored using a 10- point Likert scale assessing adherence in each of the three IPT phases. Sessions will be considered adherent to the IPT protocol if they average a score of 5 or higher and do not employ off-protocol interventions. All sessions will be audio-taped and 20 % of sessions will be selected using blocked randomization to ensure both early and late sessions are included, then transcribed and translated for IPT adherence scoring by an independent rater.

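### The therapist feasibility criterion counts only voluntary dropout, so it cannot detect trainees who never reach the score required to treat trial participants

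*Protocol article*

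**What the plan says.** The section on IPT therapists in the protocol article sets no entry bar on schooling or background: "There are no formal education or experience requirements for the community therapists who are trained to deliver IPT in this study". After a 10-day training, each therapist takes a pilot case in a run-in phase and is scored by an expert supervisor. The rule for moving on is strict: "Only those therapists who consistently score “9 s” and “10s” by the end of their IPT case will be allowed to progress". For a miss, the text provides: "Therapists who do not meet these criteria will be provided with one or two additional pilot IPT cases". It does not say what follows a miss on the last permitted case.

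The feasibility rule appears twice. Under Implementation outcomes, the therapist part is met "if 50 % or fewer of the study therapists voluntarily drop out of the training course and trial". Under Statistical analysis, Implementation, it is met "if one or fewer therapists voluntarily drop out of the training course and trial". The other conditions concern participants: recruitment against screening, attendance by completers, and attrition. In the first of the two places the last two read "if each completer attends ≥80 % of IPT sessions, attrition is 50 or fewer study participants".

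Fidelity is a separate benchmark, applied to sessions: "Sessions will be considered adherent to the IPT protocol if they average a score of 5 or higher and do not employ off-protocol interventions". The Feasibility and fidelity paragraph of the Statistical analysis says that means and proportions with 95 % confidence intervals will be compared with these benchmarks. The abstract lists feasibility and fidelity among the primary implementation outcomes.

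**The concern.** A therapist can be lost to the programme in two ways: she can leave, or she can stay and never reach the required standard. Both statements of the criterion extend to the training course as well as the trial, so the criterion is meant to cover the training stage. The word *voluntarily* then restricts it to the first kind of loss. With no entry requirement on education or experience and a demanding run-in score, the second kind is a real possibility.

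What is at stake is how a favourable therapist result is read. The Discussion says resources go to data that will inform scale-up. A clinic planning to adopt the model needs to know how many women must be trained to obtain one therapist who may treat patients, and after how many supervised pilot cases. A criterion based on resignations alone can look satisfactory while that yield is poor. The effectiveness comparison of IPT + TAU with TAU is not affected.

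**Working it through.** No sample size, power or alpha figure bears on this point, and both limits are set by decision, so there is no plan figure to reproduce. The check is whether certification failure enters the rule at all. *Certified* here means having reached the run-in score.

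**Inputs**
- T = women who start training. The document gives no number, so 6, 10 and 20 are assumed.
- V = voluntary dropouts, set to 0.
- F = trainees who stay but are never certified after all permitted pilot cases. The document gives no rate, so a range is shown.

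**Rules as stated**
- Implementation outcomes: V/T ≤ 0.5
- Statistical analysis: V ≤ 1

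F appears in neither. For comparison, the same limits were applied to loss for any reason: (V + F)/T ≤ 0.5 and V + F ≤ 1.

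| T | F | V/T | Both stated limits | (V + F)/T | 50 % limit on all loss | One-therapist limit on all loss |
|---|---|---|---|---|---|---|
| 6 | 3 | 0 % | met | 50 % | met | not met |
| 6 | 4 | 0 % | met | 67 % | not met | not met |
| 6 | 5 | 0 % | met | 83 % | not met | not met |
| 10 | 5 | 0 % | met | 50 % | met | not met |
| 10 | 6 | 0 % | met | 60 % | not met | not met |
| 10 | 8 | 0 % | met | 80 % | not met | not met |
| 10 | 9 | 0 % | met | 90 % | not met | not met |
| 20 | 10 | 0 % | met | 50 % | met | not met |
| 20 | 12 | 0 % | met | 60 % | not met | not met |
| 20 | 16 | 0 % | met | 80 % | not met | not met |
| 20 | 18 | 0 % | met | 90 % | not met | not met |

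**Denominator.** The article does not define study therapists. If the term means all trainees, the dropout proportion is V/T. If it means certified therapists only, the denominator is T − F; with T = 10 and F = 8 it is 2, and 0/2 is still 0 %. Involuntary exclusion is uncounted on either reading.

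**Other benchmarks.** Recruitment, attendance and attrition are counted in participants. Fidelity is scored per session against an average of 5, whereas the run-in requires 9s and 10s. Trial sessions come only from therapists who passed the run-in. None of these counts trainees who failed to qualify.

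**The two limits.** They also conflict with each other. The largest V allowed is 3 against 1 at T = 6, 5 against 1 at T = 10, and 10 against 1 at T = 20. The two feasibility paragraphs further differ on the participant target (220 against 200) and on attrition (50 or fewer against fewer than 50).

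**Supervised practice before trial work.** With one initial and two further pilot cases, and assuming each is a full course of 10 to 12 sessions as in the Background, the upper bound is 3 × 10 = 30 to 3 × 12 = 36 sessions per trainee. None of this enters the feasibility result.

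**The case against.** The strongest reply is that the criterion does what it says: it limits voluntary withdrawal and does not claim to estimate training yield. A competence check before treating participants is a legitimate design choice, the article lists feasibility of IPT delivery in the clinic as the outcome, and no section makes training yield an endpoint. It is also true that a condensed article may leave certification counts by pilot case, and the breakdown of costs, to the full protocol.

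Much of this stands, and it rules out three stronger readings that a reader might infer.

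- *That the run-in removes every trainee who misses the score.* It does not. The stated response to a miss is one or two more pilot cases. Exclusion after a final miss follows from the word *only*, but is not stated.
- *That the study would be declared feasible even if most trainees failed.* The therapist part is one of several joint conditions. IPT is offered to both arms, so too few certified therapists could strain recruitment, attendance or attrition. A favourable verdict is possible, not assured.
- *That the feasibility conclusion is biased upward.* The run-in does not distort a count of resignations. The fault is that the count leaves out a kind of failure.

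The reply does not remove the point itself. The restriction to voluntary departures is written into the article in both places, so it is a stated rule and not a detail left out. Because the rule reaches back to the training course, its silence on training failure is a gap in what it sets out to cover.

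**Conclusion.** The point holds in limited form. The therapist criterion cannot register trainees who stay but never reach the score needed to treat trial participants, so it can be met at any certification failure rate. This is true under both stated limits and under either reading of the denominator. It follows from the wording and does not depend on the assumed numbers; the table only illustrates it, since the document gives neither a trainee count nor a failure rate. It rests on one inference, that a trainee who misses the score on her last pilot case does not go on to treat participants.

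The consequence is confined to one condition of a primary implementation outcome. It deserves correction because the feasibility result is meant to inform scale-up.

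**What to change.** 1. Reconcile the two feasibility paragraphs so that one therapist limit applies (they now give 50 % or fewer and one or fewer), and align the participant target and attrition limit.
2. Define the denominator as all women who start the 10-day training.
3. Keep voluntary dropout as a measure of retention. Beside it, as part of the feasibility criterion, add the proportion of trainees not certified after all permitted pilot cases or lost for any reason. Keeping the two separate avoids mixing willingness to stay with competence.
4. Set a benchmark for the added proportion in advance. The document gives no basis for a value, so the authors must choose it. Carrying over the one-therapist limit would let two uncertified trainees fail the whole criterion, in a run-in designed to select.
5. State what happens after a miss on the last pilot case, and report the proportion certified after one, two and three cases.

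The cost is a wording change and a count from scores already collected to run the certification step. The downside is that the therapist feasibility figure may become less favourable. Making explicit that training and pilot-case costs of uncertified trainees enter the Cost-benefit analyses would help, but is secondary: that section excludes no training cost.

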##### Fidelity

As mentioned above, therapists will discuss each IPT session with an IPT supervisor by telephone and peer IPT supervision group onsite. During supervision, therapists will be assisted with their adherence to and application of IPT. Adherence will be scored using a 10- point Likert scale assessing adherence in each of the three IPT phases. Sessions will be considered adherent to the IPT protocol if they average a score of 5 or higher and do not employ off-protocol interventions. All sessions will be audio-taped and 20 % of sessions will be selected using blocked randomization to ensure both early and late sessions are included, then transcribed and translated for IPT adherence scoring by an independent rater.

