## Design/Methods

### Aims

We will conduct an effectiveness-implementation hybrid type I study of IPT + treatment as usual (TAU) versus TAU alone for major depressive disorder (MDD) and posttraumatic stress disorder (PTSD) among HIV+ GBV+ women receiving HIV care at FACES in Kisumu. IPT will be offered to the TAU group after the conclusion of the 12-week IPT. We will assess the effectiveness of IPT + TAU versus TAU alone for reduction of depression and PTSD symptoms, HIV viral load and improvement of ART adherence and neurocognitive functioning. We will also assess implementation parameters, including cost-benefit analyses of delivering IPT integrated within HIV clinics using non-specialist providers, fidelity and adoption of the intervention. We hypothesize that IPT + TAU will be more effective than TAU alone for remission of MDD and PTSD and that implementation analyses will show that it is delivered with high fidelity and adoption and that the benefits outweigh the costs.

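### The fidelity criterion for trial sessions is lenient beside the therapist entry standard, no trial-level benchmark defines high fidelity, and the fidelity intervals should allow for clustering by therapist

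*Protocol article*

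**What the plan says.** The abstract lists fidelity among the primary implementation outcomes, and Aims predicts that IPT will be "delivered with high fidelity and adoption".

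**Entry standard** (Interpersonal Psychotherapy (IPT) therapists). Telephone supervisors, who are the principal investigator and a co-investigator, score ten aspects of delivery on 10-point items. The rule is: "Only those therapists who consistently score “9 s” and “10s” by the end of their IPT case will be allowed to progress".

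**Session standard** (Implementation outcomes, Fidelity). Trial sessions are again rated on a scale of ten points, by phase of the therapy. The score condition reads: "Sessions will be considered adherent to the IPT protocol if they average a score of 5 or higher". A second condition rules out any intervention from outside the IPT protocol. Both conditions must be met. A random 20% of recorded sessions, covering early and late ones, goes to an independent rater.

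**Analysis** (Statistical analysis, Feasibility and fidelity). Sample means and proportions with 95% confidence intervals are to be "compared to pre-specified benchmarks (see above". How the intervals are built is not stated. For the two diagnoses, the Effectiveness section does plan a model that accounts for clustering by therapist.

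**The concern.** Three things do not fit together.

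- The two thresholds, 9-10 and 5, sit on scales of the same length, and nothing explains the difference. A low cut-off makes the share of adherent sessions a blunt measure of moderate decline, which is what matters for scale-up.
- The analysis section points back to benchmarks. Feasibility has numeric criteria for the whole trial. Fidelity has only a rule for the single session, so nothing in the article says which proportion or mean would count as high. It is also not stated whether the supervisors' or the independent rater's scores form the outcome, and the supervisors are investigators.
- Sessions by the same therapist, and with the same participant, are likely to resemble each other. An interval that ignores this overstates precision.

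At stake is whether the prediction of high fidelity can be tested and whether its precision is reported honestly.

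**Working it through.** The article gives no fidelity proportion, interval width, therapist number or ICC, so there is no figure to reproduce. What follows is illustrative.

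**Inputs from the article.** 200 participants (220 in Randomization and in the first Feasibility section), two arms, 12 sessions each, 20% sampled, cut-off 5. **Assumptions.** Equal arms with all sessions attended; session means normally distributed; 90% of sessions adherent; 6 to 20 therapists with equal loads; ICC 0.01 to 0.20.

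**1. Rated sessions.** 100 × 12 × 0.20 = 240 in the IPT arm (264 with 220 participants). If the control arm's later IPT is sampled too, 480 (528).

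**2. How often the score condition is met.** P(session mean ≥ 5) = Φ((centre − 5)/SD).

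| Centre of session means | SD 1 | SD 2 |
|---|---|---|
| 9 | >0.999 | 0.977 |
| 8 | 0.999 | 0.933 |
| 7 | 0.977 | 0.841 |
| 6 | 0.841 | 0.691 |

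A fall in the centre from 9 to 7 moves the pass share by about 2 points (SD 1) or 14 points (SD 2), while the mean score falls by 2 full points. A fall to 6 shows clearly in the share as well.

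**3. Adding the second condition.** If 98% of sessions meet the score condition and a fraction f independently goes off protocol, the adherent share is 0.98 × (1 − f): 93% at f = 5%, 88% at 10%, 78% at 20%.

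**4. Interval width.** With 240 sessions and 90% adherent, the half-width under independence is 1.96 × √(0.9 × 0.1/240) = 3.8 points. The design effect is DE = 1 + (m − 1) × ICC, where m is rated sessions per therapist. The interval widens by √DE.

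| Therapists | m | ICC | DE | √DE | Half-width (points) | Effective sessions |
|---|---|---|---|---|---|---|
| 20 | 12 | 0.01 | 1.11 | 1.05 | 4.0 | 216 |
| 20 | 12 | 0.05 | 1.55 | 1.24 | 4.7 | 155 |
| 10 | 24 | 0.10 | 3.30 | 1.82 | 6.9 | 73 |
| 6 | 40 | 0.20 | 8.80 | 2.97 | 11.3 | 27 |

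The factor √DE does not depend on the 90%; the half-widths do. With 480 rated sessions and the same therapists, DE runs from 1.23 to 16.8, a factor of 1.11 to 4.10.

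**The case against.** The strongest reply is that the two thresholds do different jobs. One certifies a therapist, on a supervisor's ratings of a pilot case. The other is a floor for a single session. A high bar for certification with a lower floor for sessions is not a contradiction. That stands: the thresholds are unreconciled, not incompatible, and no passage equates high fidelity with 9-10.

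A reader might infer more than the article supports in three ways.

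- *That high fidelity is close to assured.* A session also fails if it goes off protocol, whatever its score (step 3). Supervisors' 9s and 10s on pilot cases need not be matched by an independent rater. With no benchmark, high is undefined rather than assured. Still, the second condition catches foreign content, not weak delivery of IPT, so it does not repair the low cut-off.
- *That a decline could not be seen.* The plan already includes sample means, which would show a fall directly, and a fall to around 6 would also lower the adherent share (step 2).
- *That intervals assuming independence are planned.* The article does not describe the method, and the full protocol or analysis plan may do so. The Effectiveness section shows that the authors are aware of therapist clustering. The point about precision is therefore conditional.

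It is also fair that effectiveness is the trial's primary goal and that nothing here touches it.

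**Conclusion.** The point holds in limited form. The score cut-off is lenient relative to the entry standard, without explanation. The benchmark to which the analysis section refers is not given at trial level, so the prediction of high fidelity has no stated criterion by which it could fail. This second part rests on the text alone and needs no assumption.

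The interval part holds only if sessions are treated as independent. The direction is then clear for any positive ICC: too narrow. The size cannot be derived from the article. The range of about 1.05 to 3.0 rests on 240 rated sessions, 6 to 20 therapists and ICC 0.01 to 0.20, all illustrative beyond the session count, which itself assumes full attendance and sampling in one arm.

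**What to change.** 1. Name the independent rater's scores on the random 20% of sessions as the fidelity outcome, and keep the supervisors' scores for supervision.
2. Beside the planned mean and the share of adherent sessions, report the share at the run-in standard of 9-10. Define it on the session scale, since the article does not say that both scales use the same items. State the trial-level benchmark to which the analysis section refers, and tie any claim of high fidelity to it, not to the cut-off of 5 alone.
3. Compute the fidelity intervals with clustering by therapist, as in the Effectiveness section. If each participant stays with one therapist, this also covers repeated sessions with the same participant. With few therapists, use a small-sample correction. Report the number of therapists and the ICC.

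The cost is some wording and a little analysis; the recordings and ratings are already planned. The downside is that fidelity may look less favourable and less precise.
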